## 144 **2. Purpose of the clinical trial**

145 To explore the efficacy and safety of umbilical cord-derived MSCs in preventing severe chronic  
146 graft-versus-host disease after haploid hematopoietic stem cell transplantation

147

## 148 **3. Clinical trial design**

### 149 **3.1 Overall Design**

150 A multicenter, randomized, controlled, open clinical trial was designed to explore the efficacy and  
 151 safety of umbilical cord-derived MSCs in preventing graft-versus-host disease after haploid  
 152 hematopoietic stem cell transplantation.

### 153 3.2 Criteria

#### 154 3.2.1 Diagnostic criteria and grading criteria for acute graft-versus-host disease:

155 Acute graft-versus-host disease: a syndrome that occurs within 100 days of allogeneic hematopoietic  
 156 stem cell transplantation and is characterized by rash, diarrhea, and cholestatic hepatitis. The diagnosis  
 157 of acute graft-versus-host disease in the upper gastrointestinal tract requires endoscopic findings.

#### 158 Clinical staging criteria for Seattle aGVHD

| Staging | skin                                           | liver bilirubin | gut                                               |
|---------|------------------------------------------------|-----------------|---------------------------------------------------|
| +       | maculopapular rash <25%
body surface area   | 2-3mg/dl        | Diarrhea, 500-1000ml/day,
or persistent nausea |
| ++      | maculopapular rash 25-50%
body surface area | 3-6mg/dl        | Diarrhea, 1000-1500ml/day                         |
| +++     | Systemic erythroderma                          | 6-15mg/dl       | Diarrhea, >1500ml/day                             |
| ++++    | peeling and bullae                             | >15mg/dl        | abdominal pain and/or bowel
obstruction        |

159

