### 240     **6.3.2 Hematopoietic stem cell mobilization, collection and reinfusion**

241     The donors were given subcutaneous injection of recombinant human granulocyte colony-stimulating  
242     factor ( rhGCSF ) at  $10\text{ u g}/\text{kg} / \text{d}$  for 4 days, and peripheral blood stem cells (peripheral blood stem  
243     cells) were collected by a German Fresenius blood cell separator on d5 . blood stem cells , PBSC) . On  
244     day 6 , bone marrow collection was performed. After epidural anesthesia was performed, the donor was  
245     placed prone on the operating bed, and puncture was performed at different depths and multiple sites on  
246     the bilateral iliac ridges for collection; if it is estimated that more than 600ml of bone marrow fluid  
247     needs to be collected, the donor should be adjusted to the supine position, collected in bilateral anterior  
248     superior iliac spine puncture. If the donor and recipient ABO blood type is incompatible on the primary  
249     side, erythrocytes are removed by hydroxyethyl starch sedimentation; if the secondary side is  
250     incompatible, the bone marrow fluid needs to be centrifuged at  $4^{\circ}\text{C}$  at a low temperature, and then the  
251     plasma in the bone marrow fluid is removed with a plasma separator.

252     **6.4 Prevention of GVHD after haploid hematopoietic stem cell transplantation**

253     (1) Experimental group: On the basis of conventional GVHD prevention, UC-MSCs were infused 45  
254     days after transplantation at a dose of  $1 \times 10^6/\text{kg}$  with the interval of 14 days for 4 times.

255     (2) Control group: Beijing program for routine GVHD prevention (MMF) 0.5g q12h -7d~90d,  
256     cyclosporine (CsA) 1.25mg/kg, continuous intravenous drip; -1 day increment to 2.5mg/kg; After the  
257     patient can tolerate oral administration, it is changed to oral 5 mg/kg, and the concentration is  
258     maintained at 200-300 ng/ml; the dose is slowly reduced 180 days after transplantation; methotrexate  
259     (MTX) 15 mg/m^2 d1, 10 mg/m^2 d3, 6,11)

260     **6.5 Indicator observation**

261     (1) The incidence of severe chronic GVHD

262     (2) The incidence of II-IV acute GVHD, the incidence of chronic GVHD, OS, Post-transplant patient  
263     GRFS (GVHD-free and relapse-free survival)

264     **6.6 Therapeutic Monitoring Protocol**

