## 337 **11. Statistical Analysis Plan**

338 The Mann–Whitney tests, the chi-squared test, and Fisher's exact test were used to compare the AE  
339 between the MSC group and the control group. The competing risk model (Fine and Gray model) was  
340 used to estimate 2-year cumulative incidences and hazard ratios (HRs), with their 95% CIs, for severe  
341 cGVHD and cGVHD (competed by death and relapse) and leukemia relapse (competed by nonrelapse  
342 death). The cumulative incidence of grade II-IV aGVHD and grade III-IV aGVHD, the GRFS rate and  
343 the OS rate were estimated using Kaplan–Meier analysis and are expressed as percentages with 95%  
344 CIs. The Kaplan–Meier method, the log-rank test, and Cox proportional hazard models was used to  
345 compare the grade II-IV aGVHD and III-IV aGVHD, GRFS and OS curves between the two groups.  
346 All reported *P* values are two-sided. Statistical analyses were performed using STATA 17 (StataCorp.  
347 2021. Stata Statistical Software: Release 17. College Station, TX: StataCorp LLC)) and R (version  
348 4.4.2, R Foundation for Statistical Computing, Vienna, Austria).

349

350

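### Abdominal pain of any degree reaches the top gut stage for acute GVHD, so the staging scale is not ordered by severity and the grade III-IV analysis is open to misclassification

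*Combined protocol and SAP*

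**What the plan says.** The gut column of the Seattle staging table in section 3.2.1 has four stages:

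- **+** is "Diarrhea, 500-1000ml/day", or persistent nausea.
- **++** is "Diarrhea, 1000-1500ml/day".
- **+++** is "Diarrhea, >1500ml/day".
- **++++** is "abdominal pain and/or bowel" obstruction.

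Neither the ++++ cell nor any other part of the documents gives a degree of pain or a minimum stool volume for that stage. The only further diagnostic condition on gut disease is the sentence above the table, which says that the diagnosis "of acute graft-versus-host disease in the upper gastrointestinal tract requires endoscopic findings". It bears on diagnosing upper-tract disease and does not address how bad pain must be.

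The Seattle grading table that follows puts gut + in the grade II row only. Gut ++++ falls within the ranges of the grade III and IV rows only. Those two rows also list loss of function, ++ for grade III and +++ for grade IV. The table does not say how its columns combine.

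The grades feed two analyses. Section 6.5 lists "The incidence of II-IV acute GVHD, the incidence of chronic GVHD, OS, Post-transplant patient" GRFS as secondary indicators, and section 11 estimates and compares the "cumulative incidence of grade II-IV aGVHD and grade III-IV aGVHD".

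**The concern.** The first three gut stages rise with stool volume. The fourth drops volume and, through its and/or, lets pain alone qualify. The other ++++ cells in the same row are plainly extreme (bilirubin above 15 mg/dl; peeling and bullae), so an unqualified symptom is out of line with its neighbours.

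Two things follow. The scale can rank a milder patient above a more severe one. And the stage so assigned carries into the grading table, where it shuts the patient out of grade II. Patients with mild gut disease may then be counted in the grade III-IV analysis of section 11, or may have no grade at all. If such patients enter grade III-IV in both arms, the contrast between arms is diluted. With five centres, readings of the cell as any pain and as severe pain are both plausible at the bedside, so centres may stage differently.

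**Working it through.** The plan states no figure on this point to reproduce. The check applies the two tables literally.

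**Step 1: staging and the gut column of the grading table.** Inputs are the stool-volume cut-offs and the ++++ cell from section 3.2.1. Pain is taken as attributed to acute GVHD, and persistent nausea as absent.

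| Stool volume (ml/day) | Stage without pain | Rows admitting it | Stage with any pain | Rows admitting it |
|---|---|---|---|---|
| 0 or 300 | 0 | 0, I | ++++ | III, IV |
| 600 | + | II | ++++ | III, IV |
| 1200 | ++ | III, IV | ++++ | III, IV |
| 1600 | +++ | III, IV | ++++ | III, IV |

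So 600 ml/day with mild pain (++++) outranks 1800 ml/day without pain (+++, since 1800 > 1500). From 1000 ml/day upward pain changes the stage, but the gut cell already points to III/IV. The grade is affected at lower volumes: from II to III/IV at 500-1000 ml/day, and from 0/I to III/IV below 500 ml/day.

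**Step 2: do the other columns have to match?** The grading table does not say, so three readings were tried.

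- *Gut column alone:* gut + gives grade II; gut ++++ gives III or IV.
- *Gut and loss of function:* gut ++++ gives III with function ++ and IV with function +++. With function 0 or + it fits no row.
- *All four columns:* there are 5 skin x 5 liver x 4 function = 100 combinations for each gut stage. Gut + gives grade II in 4 x 1 x 1 = 4 and no row in 96. Gut ++++ gives grade III in 3 x 3 x 1 = 9, grade IV in 4 x 3 x 1 = 12, and no row in 100 - 9 - 12 = 79.

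On no reading is gut ++++ grade II. Whenever a grade is returned, gut + means II and gut ++++ means III or IV. The combination counts describe the tables; they are not patient frequencies.

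**Step 3: which analyses are touched.** A move from II to III-IV changes the grade III-IV analysis and leaves II-IV as it was. A move from 0/I to III-IV changes both. GRFS may be affected, but its GVHD component is not defined. Severe chronic GVHD is graded on the separate NIH scale in section 3.2.2.

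**Step 4: size, as an illustration only.** Section 1.1 gives about 50% for grade II-IV. Everything else here is assumed: 30-35% of patients in grade II, 30-50% of those with gut +, 20-50% of those with pain, a true III-IV rate of 15%, and the gut column governing.

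- Low end: 0.30 x 0.30 x 0.20 = 1.8 percentage points; 1.8 / 15 = 12% relative.
- High end: 0.35 x 0.50 x 0.50 = 8.75 percentage points; 8.75 / 15 = 58% relative.

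The spread shows how little the documents fix. The figures also leave out patients below 500 ml/day.

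**The case against.** The strongest reply is that the grade shift is not certain. Rows III and IV also list loss of function ++ and +++, and a patient with mild cramps is the least likely to have either. If that column binds, the patient is not moved to III-IV but left without a grade. This stands, and it limits the point: a reader might infer that mild gut disease as such is moved from grade II to III-IV. The documents support this only for patients with pain attributed to acute GVHD, and only if the gut column governs. Even so, the alternative leaves the case ungradable, which also needs repair.

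Second, section 3.2.1 characterises acute GVHD by rash, diarrhoea and cholestatic hepatitis, so pain must first be attributed to the disease. That narrows the group affected. It does not supply a severity threshold once attribution is made.

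Third, a reader might infer that unblinded clinicians bias the comparison. The documents do not establish that. Section 6.6 speaks of clinicians blinded to allocation, although the items it lists are blood, organ-function and viral tests, marrow examinations, and MRD and mutation testing; GVHD staging is not among them. The same cell applies to both arms. What remains is that pain is patient-reported in an open trial, and blinded GVHD staging is not stated.

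Fourth, grade III-IV appears only as an analysis in section 11; the indicator in section 6.5 is II-IV. This is correct and keeps the weight moderate.

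Finally, the fault might be folded into repair of the grading table, whose grade IV row uses a five-plus stage absent from the staging table. That is a separate error; correcting it would leave the ++++ gut cell as it is.

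**Conclusion.** The concern holds in a limited form. The gut staging column is not ordered by severity, because pain of any degree attributed to acute GVHD gives ++++ at any stool volume. Such a patient cannot be grade II under the grading table. The patient becomes III-IV if the gut column governs, or can fit no row if loss of function also binds. Grade III-IV is therefore open to misclassification, and II-IV possibly so through patients below 500 ml/day. The primary endpoint is unaffected.

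The size is unknown, because the documents give no rate of abdominal pain. The 12% to 58% range should not be read as this trial's error: it rests on assumed rates and on every gut + patient with pain being moved. No between-arm bias is shown. The change is worth making because the rule as stated misorders patients and is cheap to correct.

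**What to change.** - In the ++++ gut cell, qualify pain by severity, for example severe abdominal pain attributed to gut acute GVHD. Keep bowel obstruction sufficient on its own, so that obstruction without diarrhoea still qualifies.
- State that lesser pain does not raise the stage set by stool volume.
- Reconcile the cell with the grading table: say how the columns combine, whether loss of function is a binding condition, and what the five-plus entry in the grade IV row means.
- The synopsis gives a study period ending in February 2022. If data are already collected, state the rule that was applied. Where stool volumes were recorded, re-derive grade III-IV with pain-only ++++ cases staged by volume, as a sensitivity analysis.

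Cost: one table cell, one CRF field for pain severity and one extra analysis. No new procedure is needed.

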#### 160 Seattle aGVHD

| Grading                 | skin    | liver    | gut      | loss of
function |
|-------------------------|---------|----------|----------|---------------------|
| 0 (none)                | 0       | 0        | 0        | 0                   |
| I (light)               | +~+++   | 0        | 0        | 0                   |
| II (moderate)           | +~++++  | +        | +        | +                   |
| III (severe)            | ++~++++ | ++~++++  | ++~++++  | ++                  |
| IV(Life
Threatening) | +~+++++ | ++~+++++ | ++~+++++ | +++                 |

161

#### 162 3.2.2 Diagnostic criteria and grading criteria for chronic graft-versus-host disease

163 Chronic graft-versus-host disease: It occurs 100 days after transplantation, or is diagnosed as chronic  
 164 GVHD with clinical manifestations of acute GVHD , without waiting for testing or other organ damage.  
 165 The NIH working group believes that at least one chronic GVHD diagnostic feature and one unique  
 166 manifestation can be diagnosed as chronic GVHD.

#### 167 US NIH Chronic GVHD Consensus

| Level          | Degree of involvement                                                                                         |
|----------------|---------------------------------------------------------------------------------------------------------------|
| mild cGVHD     | Damage to only 1 or 2 organs or sites (excluding lungs), no significant
functional impact (level 1 damage) |
| Moderate cGVHD | At least 1 organ or site is damaged, but most of the function is still (level 2                               |

|              |                                                                                                                                                                                                                              |
|--------------|------------------------------------------------------------------------------------------------------------------------------------------------------------------------------------------------------------------------------|
| Severe cGVHD | damage), or 3 or more organs or sites are damaged, but function is incomplete (level 1 damage), lung Partial damage level 1
Most of the patient's function is impaired, and the degree of lung damage is grade 2 or above |
|--------------|------------------------------------------------------------------------------------------------------------------------------------------------------------------------------------------------------------------------------|

168

169

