| Observation period       | (1) Real-time observation of the occurrence of acute and chronic GVHD after transplantation;
(2) Follow-up: relapse, death and HSCT related complication                                                                                                                                                                                                                                                                                                                                                                                                                                                                                              |
| Primary Endpoint         | Severe chronic GVHD                                                                                                                                                                                                                                                                                                                                                                                                                                                                                                                                                                                                                                      |
| Secondary Endpoint       | Chronic GVHD, acute GVHD, Overall survival (OS), GVHD-free and Relapse-free survival (GRFS).                                                                                                                                                                                                                                                                                                                                                                                                                                                                                                                                                             |

|                   |                                                                                            |
|-------------------|--------------------------------------------------------------------------------------------|
| Safety evaluation | Incidence of adverse events (AE) and severe AE during 45 days to 100 days after haplo-HSCT |
| Study period      | 2016.4-2022.2                                                                              |

29

30

31

32  
33  
34  
35  
36  
37  

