## 301 **8. Sample Size**

302 Sample-size estimates were based on the assumption of a log-rank test for the between-group  
303 comparison of the primary end point, the incidence of cGVHD. In the preliminary experiment, the  
304 cumulative incidence of severe cGVHD in the experimental and control group was 5.7% and 15%,  
305 respectively. We assumed 2 years for enrollment and 5 years for follow-up. A sample size of 142 total  
306 patients was calculated with a two-sided type II error of 0.05 and a statistical power of 90% for the

307 cumulative incidence of cGVHD. Considering the expected rate of loss to follow-up (10%), we decided  
308 to include 158 patients, with 79 patients in each arm. The sample size calculation was performed with  
309 PASS version 15 software (NCSS, Kaysville, UT).

310

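### Read as written, severe cGVHD requires lung damage of grade 2 or above, so major non-lung disease with no lung involvement fits no grade and is not a primary event

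*Combined protocol and SAP*

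**What the plan says.** The synopsis of the combined protocol and SAP names the primary endpoint as "Severe chronic GVHD". Sections 5.2 and 6.5 list the same outcome first. No section other than 3.2.2 says what makes chronic GVHD severe. The table there, headed as the US NIH consensus, has three rows:

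- **Mild:** "Damage to only 1 or 2 organs or sites (excluding lungs), no significant" effect on function, at level 1.
- **Moderate:** "At least 1 organ or site is damaged, but most of the function is still (level 2" damage), "or 3 or more organs or sites are damaged, but function is incomplete (level 1 damage), lung Partial damage level 1".
- **Severe:** most of the patient's "function is impaired, and the degree of lung damage is grade 2 or above".

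In the extracted text a page break pushes the end of the moderate row into the severe cell. That comes from the extraction and I do not count it against the plan. The severe sentence itself is unbroken.

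Section 8 plans the trial on preliminary severe-cGVHD rates of 5.7% (experimental) and 15% (control). It mentions no lung restriction, does not say how those cases were graded, and gives no time point for the rates. The enrolment target is 158, with 79 per arm.

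**The concern.** The severe row joins two conditions with *and*. On that wording, lung damage of grade 2 or above is necessary for a primary event. Severe disease confined to other organs could never count, however disabling. Neither lower row would take such a patient, because mild and moderate are both worded for patients whose function is largely preserved. The patient would be left ungraded.

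The gap is in the definition of the primary endpoint, so it decides what question the trial answers. It also leaves each centre to choose a reading. The synopsis lists five centres, section 3.1 describes an open trial, and no central adjudication or tie-break rule is given. Settling the reading after outcomes are known would be open to bias.

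**Working it through.** There is no stated figure to reproduce for a definition, so I applied the rows to patient profiles.

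**1. Profiles against rows.** Assumptions: the worst organ sets the grade, and the severe row's loss of function means loss of most function in at least one organ.

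| Profile | Mild | Moderate | Severe (*and*) | Severe (*or*) |
|---|---|---|---|---|
| A. Most function lost in a non-lung organ, no lung involvement | No: function affected | No: function not mostly kept, not level 1 only, no lung damage | No | Yes |
| B. As A, with lung level 1 | No | Only if lung level 1 alone is enough | No | Yes |
| C. Lung grade 2, most function kept | No: lungs excluded | Yes: the level 2 limb does not exclude the lungs | No | Yes |
| D. As A, with lung grade 2 or above | No | No | Yes | Yes |

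Under *and*, profile A has no row. Profile B depends on how the moderate lung item is read, since no connective precedes it. Profile C is graded moderate.

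**2. Count over a grid.** Assumption: three non-lung organs and the lung are each scored 0 to 3, where 3 is my label for loss of most function. The protocol's table does not define such a score. Profiles with any involvement: 4⁴ − 1 = 255.

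- Lung 0, at least one non-lung organ at the top score (A): 4³ − 3³ = 64 − 27 = 37.
- Lung 1, same condition (B): 37.
- Unclassified under *and*: 37 + 37 = 74, or 37 if lung level 1 alone makes a case moderate.
- If, in addition, a second organ at level 2 were enough for moderate whatever the worst organ shows, the A profiles with no score of 2 would still be ungraded: 3³ − 2³ = 27 − 8 = 19.
- Lung 2, no non-lung organ at the top score (C): 3³ = 27, graded moderate under *and*.
- Unclassified under *or*: 0.

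These are counts of possible patterns. They say nothing about how often each occurs in patients.

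**3. Overlap under *or*.** The 27 C profiles would then satisfy both moderate (level 2 limb) and severe. The 37 B profiles would also satisfy both if lung level 1 alone is enough for moderate. Changing the connective makes the table exhaustive but does not make its rows exclusive.

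**4. Scale of the endpoint.** Inputs are the section 8 rates and 79 per arm.

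- Experimental: 79 × 0.057 = 4.5 events.
- Control: 79 × 0.15 = 11.85 events.
- Total: about 16.4. Difference: about 7.3.

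This takes all 158 patients as observed over whatever period the rates refer to.

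**The case against.** The strongest reply is that this is a rough translation of a two-item list. The moderate row's lung item has no connective at all and is naturally read as an alternative, so it looks selective to hold the severe row strictly to its *and*. The table also names its source, and clinicians who know that source may have graded from it. This stands as far as intent goes: the documents do not show that the joint rule was meant or used. It does not remove the defect, because this table is the operative endpoint rule and nothing elsewhere in the document overrides it.

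A reader might go further and infer that the trial measured only severe lung disease, or that it lost a calculable amount of power. The documents support neither. They contain no grading data and no lung share of severe cases. If the preliminary 5.7% and 15% were graded with this same table, those rates already reflect the wording and no shortfall follows.

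A reader might also infer that lung grade 2 with function otherwise kept is ungraded. It is not: moderate takes it, since only the mild row excludes the lungs.

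Section 6.6 mentions clinicians blinded to allocation up to one year. The assessments listed there are blood, viral, marrow and residual-disease tests, with no cGVHD grading, and blinding does not settle an ambiguous rule. Equally, nothing shows that centres did grade differently.

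**Conclusion.** The concern holds in this form. The sole definition of the primary endpoint, read literally, makes lung damage of grade 2 or above a requirement. It leaves major non-lung impairment without lung involvement outside all three grades, and so outside the primary event count. Cases with lung grade 2 and most function kept are moderate rather than severe. Of the two readings of the severe row, only the alternative one gives every patient a grade.

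The effect on events and power cannot be quantified from the documents. What can be said is that about 16 events are expected at the planning rates, with about 7 separating the arms, so moving a few patients across the severe boundary could change the result. The gap for profile A does not depend on the grid: a single badly affected non-lung organ and nothing else is enough to show it. The profile counts do rest on the assumed scoring. The finding is an incomplete endpoint rule, not evidence that any patient was misgraded.

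**What to change.** Rewrite the severe row so that its two conditions are alternatives, with the sponsor confirming the wording against the consensus it names. State how overlaps are resolved, so that lung grade 2 with function kept, and lung level 1 with major impairment elsewhere, each fall in one row only. Apply that single rule to primary-endpoint grading at all five centres, and settle it before severity is analysed.

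If any patient was graded under the joint reading, re-grade from available records and report the joint reading as a sensitivity analysis.

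The text change is small. The cost lies in any re-grading, which is possible only where organ-level findings were recorded. The monitoring list in section 6.6 does not mention cGVHD organ scoring, so this should be checked rather than assumed.
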